### Physicians’ perceptions of the reminders

Physicians get the opportunity to give their opinion when a reminder is triggered. Physicians can choose between useful, not useful, or no advice. They can give feedback for each reminder and can indicate if they wish to block the reminder in the future.

### Data collection

Data will be automatically extracted from the EMR of the family physician for all patients who satisfy the eligibility criteria. Data will be extracted at five points in time: before the start of the study, at 3 months, at 6 months, at 9 months, and at 12 months. All outcomes can be reliably determined from the electronic medical records. When a physician closes HealthOne, a reminder will be shown to export the data. The family physician can visualize the data and has to confirm if he agrees to export. Modifications to this file cannot be made by the physician.

Identification data of the patient will be manually converted to an output code via a hashing program installed on the computer of the family physician. Data will be sent by mail to an independent third person. This person will be responsible for uncoupling the identifiable data of the family physician (name and e-mail address) from the patient data and the data related to the actual use of the system. A meaningless code will be allocated to the physician’s data and its corresponding patient and use data. The coupling between these data will be exclusively possessed by this person and will be used to couple the data at the different points in time.

These coded data will be sent securely to the researcher. Patient data will be sent to the researcher at the five interim analysis points. Data concerning EBMeDS use will be sent once to the researcher at the end of the study period after patient data are analyzed. Data related to system use will be used to explore possible relationships between the patient outcomes and the actual use of the system. As there is only one file of actual use for the physicians in the intervention group, the researcher would not be blinded if these data were sent together with the patient data.

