### Primary and secondary outcomes

Primary outcome is the one-year pre- to post-implementation change in HbA1c.

Secondary outcomes are the one-year differences in cholesterol levels and systolic and diastolic blood pressure. A composite patient score and a composite process score are calculated representing the change in diabetes (process) control and associated cardiovascular risk [19]. The composite patient score consists of reaching the evidence-based targets for glycated hemoglobin, blood pressure (systolic and diastolic), and cholesterol. The process composite score consists of meeting the evidence-based targets of the number of blood pressure measurements, the number of laboratory results of HbA1c, cholesterol and micro-albuminuria, a prescription of statin (yes/no), if high cardiovascular risk a prescription of aspirin/clopidogrel (yes/no), if hypertension or nephropathy ACE inhibition/sartan (yes/no).

Outcomes that cannot be reliably detected from the electronic medical records such as smoking status, and feet and eye examinations are excluded from the composite scores, as well as outcomes in which family physicians’ influences are minimal (*e*.*g*., BMI, physical activity, etc.).

Outcomes of the composite scores with their respective targets are shown in Table 1. Recommendations and targets are based on the diabetes guidelines of Domus Medica [20] and the Belgian ‘Zorgtraject diabetes’ [21].

**Table 1 T1:** Variables included in the composite scores

***Variable***	***Process target***	***Maximum score per period****	***Clinical target***	***Maximum score per period***^**†**^
HbA1c	Quarterly	2	< 7%	1
Blood pressure	Quarterly	2	< 130/80 mm Hg	1
Cholesterol (LDL, HDL, Total)	Annual	1	LDL < 100 mg/dL	1
Microalbuminuria check	Annual	1		
A prescription of statin	Yes/no	1		
If high cardiovascular risk, a prescription of aspirin/clopidogrel	Yes/no	1		
If hypertension or nephropathy, ACE inhibition/sartan	Yes/no	1		
Total		9		3

*Maximum score for process composite per period = 9 (7 variables).

^†^ Maximum score for patient composite per period = 3 (3 variables).

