### Sample size

Based on the data in the literature, a mean difference of 0.3% in HbA1c change could be considered clinically significant (SD of HbA1c change 1.3%) [23-25]. To detect a mean difference of 0.3% in HbA1c change at four post-treatment occasions, with a two-sided unpaired *t*-test, a 5% family-wise significance level and Bonferroni correction for multiple testing, 1:1 allocation and a power of 80%, a sample size of 463 patients in each group will be necessary, assuming a withdrawal rate of 10%. Additional adjustment for clustering of patients within physician practices by the design effect [26], assuming 10 patients per cluster and an intra-class correlation coefficient of 0.047 based on data in the literature [27], leads to a sample size of 659 patients in each arm. Sample size calculations were based on historical data. They can be adjusted after baseline registrations if correct standard deviations and intra-cluster correlation coefficients are known. Sample size calculation was performed using SAS software.

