### Data analysis

Descriptive statistics will be provided regarding baseline variables of the patients and the family physicians. Intervention and control groups will be compared regarding baseline variables to evaluate the randomization. Linear mixed models will be used for continuous patient-level variables, with a random intercept to account for clustering of patients within physician practices. Logistic regression models based on generalized estimating equations (GEE) to account for clustering will be used for binary patient-level variables.

Differences between intervention and control groups regarding continuous outcome measures (change versus baseline in HbA1c, cholesterol levels, and blood pressure) will be assessed using linear mixed models (multilevel regression models) with random intercepts for physician practices and random intercepts for patients to account for repeated measurements over time. The primary fixed effect of interest will be the difference between intervention and control group, which will be tested at each time point (3 m, 6 m, 9 m and 12 m). If important differences in baseline characteristics are demonstrated between both groups, we will account for that by including the relevant variables in the model.

Differences between intervention and control groups regarding three-level composite scores (worsening, unchanged, improvement) will be assessed using random-effects proportional odds models, or, in case the proportional odds assumptions do not hold, baseline-category logits models, with random intercepts for physician practices and random intercepts for patients to account for repeated measurements over time. As with the analysis of continuous outcomes, differences between intervention and control groups will be tested at all time-points, and correction for imbalance in baseline characteristics will be applied if indicated.

To study the effect of the actual use of the EBMeDS system on the outcome measures, models similar to those described above will be used for analyzing the effect of intervention. However, they will now include a measure for the use of EBMeDS as the main explanatory variable, and will restrict analysis to the data obtained in the intervention group.

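### HbA1c is seen only when routine care orders a test, which the intervention may make more frequent; the change-score model should be replaced by one that conditions on baseline, and the 10% loss allowance checked

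*Protocol article*

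**What the plan says.** Under Primary and secondary outcomes the protocol states: "Primary outcome is the one-year pre- to post-implementation change in HbA1c". Under Data collection, values are extracted automatically from the physician's record at five time points, with the assurance that "All outcomes can be reliably determined from the electronic medical records". No HbA1c test ordered by the study is described.

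The process composite includes "the number of laboratory results of HbA1c, cholesterol and micro-albuminuria", and Table 1 sets a quarterly target for HbA1c. The Ethics section says that reminders appear when a patient's data depart from target. Under Participants and setting, a diagnosis code or a diabetes prescription is enough for inclusion, so a patient can enter without an HbA1c value.

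Data analysis applies linear mixed models to "change versus baseline in HbA1c, cholesterol levels, and blood pressure", with random intercepts for practice and patient. The arm difference is tested at 3, 6, 9 and 12 months. Baseline variables enter the model only if important differences between the groups are found.

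The sample size is 659 per arm, "assuming a withdrawal rate of 10" per cent. Only the standard deviation and the intra-cluster correlation are named as inputs that may be revised after baseline.

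**The concern.** Whether the primary outcome exists for a patient depends on care after randomization, and the trial hopes to change that care. If reminders raise testing, the intervention arm is analysed on a broader set of patients than the control arm. Randomization does not protect a comparison of those two sets.

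The choice of response makes this worse than it need be, in two ways.

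- A change score cannot be formed without a baseline value, so such patients drop out of the primary analysis.
- A change score does not condition on baseline HbA1c. Patients with high baseline values tend to fall and those with low values to rise. If testing at follow-up is related to baseline HbA1c and its frequency differs by arm, mean change differs between arms with no treatment effect.

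The adjustment rule is not a reliable safeguard. It is triggered by comparing the groups at baseline, where randomization should make them alike. The imbalance in question arises later, among those who are tested.

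Bias in this contrast would also enter the interim rule, which ends the trial when a 0.3% difference is reached. Separately, a patient who stays registered but untested has not withdrawn in the ordinary sense, so it is unclear whether the 10% covers such patients.

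**Working it through.** **1. The plan's own figure.** Inputs from Sample size: difference 0.3, "SD of HbA1c change 1.3" per cent, two-sided, 0.05/4 = 0.0125 per test, power 80%.

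- n = 2 × [1.3 × (2.498 + 0.842) / 0.3]² = 419 per arm. The exact t-test gives 421.
- 421 × 1.10 = 463.1, against the stated 463.
- Design effect 1 + (10 − 1) × 0.047 = 1.423, and 463 × 1.423 = 658.8, against the stated 659.

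The arithmetic reproduces.

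**2. Power with 659 per arm if a share m has no usable HbA1c change.** The documents give no value for m, so it is an assumption shown as a range.

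Effective n = 659 × (1 − m) / DE. Power = Φ(0.3 / [1.3 × √(2 / effective n)] − 2.498).

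DE is either kept at 1.423 or recalculated on the measured patients as 1 + (10(1 − m) − 1) × 0.047.

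| m | Effective n, DE 1.423 | Power | DE recalculated | Effective n | Power |
|---|---|---|---|---|---|
| 10% | 416.8 | 80% | 1.376 | 431.0 | 81% |
| 20% | 370.5 | 74% | 1.329 | 396.7 | 77% |
| 30% | 324.2 | 67% | 1.282 | 359.8 | 73% |
| 40% | 277.9 | 59% | 1.235 | 320.2 | 66% |

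For 80% power, 20% loss would need 746 per arm (697 with DE recalculated) and 40% would need 994 (863).

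**3. Bias from unequal testing, with no true effect.** Suppose a patient is tested when a normally distributed propensity exceeds a cut-off, with proportion p tested. Let r be the correlation of that propensity with HbA1c change. Among the tested, mean change is shifted in size by 1.3 × r × φ(z)/p, where z is the cut-off. The ratio φ(z)/p is 0.644 at p = 60%, 0.350 at 80% and 0.195 at 90%. The testing rates and r = 0.1 to 0.3 are assumptions.

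- Within one arm at 80% tested: 1.3 × 0.1 × 0.350 = 0.05, up to 1.3 × 0.3 × 0.350 = 0.14.
- 60% versus 80% tested: 1.3 × r × (0.644 − 0.350) = 0.04 to 0.11 (0.115 unrounded).
- 80% versus 90% tested: 1.3 × r × (0.350 − 0.195) = 0.02 to 0.06.
- Equal rates: zero.

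This is the bias in a comparison of means at one time point among those tested.

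**4. What conditioning on baseline does.** Let testing depend on baseline HbA1c only, and let k be the correlation of the propensity with baseline. Then r in size = k × |correlation of baseline with change|. If that last correlation were −0.5 (an assumption), k = 0.2 to 0.6 would give the r = 0.1 to 0.3 used above. Given baseline, testing carries no further information about change. The arm contrast conditional on baseline is then zero when there is no effect, and the whole shift in step 3 disappears. If testing also depends on the unseen follow-up value, some shift remains.

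**The case against.** Several objections have force.

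- **The reliability statement.** A reader might infer that it is false. It more naturally describes which variables the record captures, as the counterpart to leaving smoking status and foot and eye examinations out of the composites. It does not claim that every patient has a value at every time point. That stands.
- **Partial follow-up.** A reader might infer that the planned model discards patients with some follow-up values missing. It does not, because a mixed model uses the values that exist. It also borrows from 3, 6 and 9 months, so step 3 need not equal its bias at 12 months. The loss concerns patients with no baseline.
- **Missing baselines.** These arise before the intervention starts. They cost numbers and representativeness but do not themselves create an arm difference.
- **The testing gap is inferred.** No HbA1c-testing reminder is listed, and controls have the Evidence Linker with similar guideline content. The gap may be small.
- **The 10% allowance.** A reader might infer that it is wrong. Patients give no individual consent, so the figure may be meant as a general loss allowance, and nothing in the document shows it to be too low.
- **Exports.** The protocol says: "The family physician can visualize the data and has to confirm if he agrees to export". A reader might infer that loss by practice differs by arm, or that a later cumulative export would recover a refused one. The documents do not show the first. The second fails at 12 months, where no later export is planned, and it would bear on the physician's agreement.
- **Missing-data methods.** These may be in an analysis plan not shown, and their absence is not the point here.

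What remains is a stated method, the change score with conditional adjustment, applied to an outcome whose observation the intervention may influence.

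**Conclusion.** The concern holds in a limited form. HbA1c is observed only through routine testing, testing frequency is a target of the intervention, and the stated model neither keeps patients without a baseline value nor routinely conditions on baseline HbA1c. It is therefore open to bias if testing depends on baseline HbA1c and differs between arms.

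Neither condition can be confirmed from the document. The 0.02 to 0.12 points, or about 7% to 38% of the 0.3 target (0.02/0.3 and 0.115/0.3), rest on assumed testing rates and correlations. The direction is open, and the bias is zero if testing rates are equal. The power range of roughly 77% to 59% is likewise a scenario for 20% to 40% without a usable value, at the plan's 0.0125 level. It shows that the allowance is worth checking, not that it has failed.

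**What to change.** - **Primary model.** Replace change from baseline by HbA1c level at baseline, 3, 6, 9 and 12 months as the response. Use a common baseline mean across arms, an unstructured within-patient covariance and practice random effects. Take the 12-month arm contrast as primary, which matches the stated one-year outcome. Patients without a baseline stay in, and the contrast conditions on baseline and earlier values whether or not imbalance is found. The cost is a change of analysis wording.
- **Remaining limit.** This does not handle testing driven by HbA1c values that nobody sees. Testing rates by arm and a delta-adjusted sensitivity analysis for untested patients can be reported for that purpose, in the analysis plan if preferred.
- **Loss allowance.** At the baseline extraction, count the share of patients without a usable HbA1c. Add loss to the inputs open to revision beside the standard deviation and intra-cluster correlation, and restate power if the share exceeds 10%. The extraction is already planned, so this costs one count. If the share is larger, the price is more practices or a plain statement of lower power.

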### Sample size

Based on the data in the literature, a mean difference of 0.3% in HbA1c change could be considered clinically significant (SD of HbA1c change 1.3%) [23-25]. To detect a mean difference of 0.3% in HbA1c change at four post-treatment occasions, with a two-sided unpaired *t*-test, a 5% family-wise significance level and Bonferroni correction for multiple testing, 1:1 allocation and a power of 80%, a sample size of 463 patients in each group will be necessary, assuming a withdrawal rate of 10%. Additional adjustment for clustering of patients within physician practices by the design effect [26], assuming 10 patients per cluster and an intra-class correlation coefficient of 0.047 based on data in the literature [27], leads to a sample size of 659 patients in each arm. Sample size calculations were based on historical data. They can be adjusted after baseline registrations if correct standard deviations and intra-cluster correlation coefficients are known. Sample size calculation was performed using SAS software.

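### The primary outcome is the one-year HbA1c change, but alpha is split equally over four visits and all four are tested, so the plan does not fix what counts as success

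*Protocol article*

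**What the plan says.** Four places in the protocol article bear on this.

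- **Primary and secondary outcomes** (and the abstract) name one quantity at one time: "Primary outcome is the one-year pre- to post-implementation change in HbA1c".
- **Sample size** is built on four tests: "To detect a mean difference of 0.3% in HbA1c change at four post-treatment occasions", "with a two-sided unpaired *t*-test", and "a 5% family-wise significance level and Bonferroni correction for multiple testing". Four tests at a family-wise 5% give 0.05/4 = 0.0125 each.
- **Data analysis** makes the difference between the groups the main fixed effect, "which will be tested at each time point (3 m, 6 m, 9 m and 12 m"). The per-test level is not given there.
- **The abstract and the text after Table 1** treat months 3, 6 and 9 as interim analysis points. They allow the trial to end at one of them when the mean difference in HbA1c change reaches 0.3%. No p-value, boundary or alpha level is attached to that rule.

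**The concern.** These sections fit together in more than one way. The outcomes section reads as one test at month 12. The sample size and analysis sections read as four tests with alpha shared equally among them. No sentence says which results would support the primary claim.

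Two things follow. If success at any visit counts, a difference present at month 3 and gone by month 12 could be reported as a positive primary result, although the stated outcome is the one-year change. If only month 12 counts, three quarters of the alpha is assigned to visits that are not the primary outcome. Choosing between these readings after the data are seen would weaken the main conclusion of the trial.

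The early-termination rule adds to the problem. It acts on the same outcome at three of the same visits, but by a criterion unrelated to the 0.0125 level.

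**Working it through.** **Inputs, all from Sample size:** difference 0.3, SD of change 1.3, power 80%, 1:1 allocation, family-wise 5% over four tests, 10% withdrawal, 10 patients per cluster, ICC 0.047, and totals of 463 and then 659 per arm.

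**1. Reproducing the plan's figures.** With n = 2(SD/δ)²(z₁₋α/₂ + z₀.₈)² per arm:

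- α = 0.0125: 2 × (1.3/0.3)² × (2.498 + 0.842)² gives 419; the exact t-test gives 421.
- α = 0.05: 2 × (1.3/0.3)² × (1.960 + 0.842)² gives 295; the exact t-test gives 296.
- Withdrawal: 421 × 1.1 = 463.1, the plan's 463.
- Design effect: 1 + 9 × 0.047 = 1.423, and 463 × 1.423 = 658.8, the plan's 659.

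The plan's numbers come out at 0.0125 and not at 0.05, so the four-way split did set the sample size.

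**2. Power for month 12 at 659 per arm.** Effective number per arm: 659 × 0.9/1.423 = 416.8. Standard error: 1.3 × √(2/416.8) = 0.0900. Standardised effect: 0.3/0.0900 = 3.33.

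| Level at month 12 | Power (normal) | Power (t-test) |
|---|---|---|
| 0.0125 | 79.8% | 79.6% |
| 0.05 | 91.5% | 91.4% |

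The difference is about 12 points.

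**3. Size needed for a single 5% test.** Multiplying for withdrawal, as the plan does: 296 × 1.1 × 1.423 = 463 per arm. Dividing instead: 296/0.9 × 1.423 = 468 per arm. Against 659, the equal split accounts for 191 to 196 patients per arm.

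**4. How far the readings of success differ.** The protocol gives no correlation between visits and no time course of effect. Assuming the same 0.3 effect at every visit, correlations of 0.3 to 0.9, and 0.0125 per test:

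- month 12 alone: about 80% power;
- any of the four: about 88% to 98%.

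**5. The termination rule against the 0.0125 level.** With all 416.8 effective patients per arm, significance at 0.0125 needs an observed difference of 2.498 × 0.0900 = 0.225. An observed 0.3 corresponds to a two-sided p of about 0.0009. With only half the data at a look (an assumption), an observed 0.3 gives p of about 0.018, which would miss 0.0125. The rule is therefore not the Bonferroni boundary in another form, and the error it spends depends on how complete the data are.

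**6. If the looks keep a small share of alpha.** Leaving about 0.043 for month 12 (an assumed figure) gives power of about 90%.

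**The case against.** The strongest reply is that the sections describe one design: a one-year outcome, looked at four times with possible early termination, and alpha divided by four to pay for the looks. Bonferroni over four looks is valid, if conservative, so alpha on the early looks would not be wasted. This is a plausible reading, and it must be allowed for in any remedy. But the sample size section speaks of detecting a difference at four occasions and does not mention stopping, while the stopping rule does not mention a significance level. The reader has to supply the link.

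It can also be said that the main fixed effect in Data analysis is only a model coefficient, since the same passage covers cholesterol and blood pressure. That is fair: the wording does not declare four co-primary outcomes. It does not say which of the four tests is decisive either. A separate analysis plan could add detail, but it would not make these sections agree as written.

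Two stronger readings are tempting and are not supported:

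- **The trial is underpowered.** It is not. It delivers about 80% at the level it was sized for. The 12 points are power forgone at the same sample size, not a shortfall.
- **Each visit would be tested at 5%, inflating the family-wise error.** Data analysis does not repeat the per-test level, but Sample size states a 5% family-wise level with Bonferroni. The silence of one section does not override that. If any of four at 0.0125 is intended, family-wise error over those four tests is controlled; the difficulty is then that success is no longer the one-year outcome.

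**Conclusion.** The point holds as a mismatch between the stated primary outcome, the alpha allocation, the tests and the termination rule. The text does not fix whether success is month 12 alone or any of four visits, and the possible reason for the split, the interim looks, is neither stated nor tied to the rule for ending the trial.

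Its size, under the plan's own assumptions (difference 0.3, SD 1.3, ICC 0.047, 10 per cluster, 10% withdrawal), is about 80% against about 91% power for month 12 at 659 per arm. Put the other way, a single 5% test needs about 463 to 468 per arm. The any-of-four power and the figure for retained interim alpha rest on assumptions that are not in the document. The matter should be settled before outcome data are seen.

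**What to change.** 1. In Primary and secondary outcomes and in Data analysis, name the 12-month between-group contrast from the mixed model as the sole confirmatory test. Report the 3-, 6- and 9-month contrasts as secondary estimates with confidence intervals and no claim of success.
2. Reconcile the termination rule after Table 1 with this, in one of two ways:
   - the interim looks carry no efficacy claim, and month 12 is tested at two-sided 5% (power about 91% at 659 per arm); or
   - the looks use a pre-stated alpha-spending boundary in place of both Bonferroni and the 0.3% point-estimate rule, leaving most of the 5% for month 12 (about 90% power if roughly 0.043 to 0.045 remains, an assumed figure).
3. Restate the level and power in Sample size to match.

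This is more than rewording: assigning the full 5% to month 12 while leaving the present termination rule untouched would give the looks no alpha at all. The price is that no confirmatory claim can be made at 3, 6 or 9 months outside the boundary. No additional patients are needed.

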## Methods

The study is a cluster-randomized trial with before/after measurements conducted in Belgian family medicine. A cluster design is necessary to minimize contamination that might occur if individual patients were randomized. Randomization will be performed at practice level; the intervention will happen at physician level; and data will be analyzed at patient level, in a multilevel analytical approach. The follow-up period of the study will be 12 months.

Physicians’ practices will be randomly assigned to the intervention or control group in a 1:1 ratio, to receive either the EBMeDS reminders or to follow the usual care process.

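### The 80% power at 659 patients per arm assumes about 10 patients per practice, but every eligible patient is extracted and neither the target nor the re-sizing clause covers practice size

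*Protocol article*

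**What the plan says.** The Methods section makes the practice the unit of allocation: "Randomization will be performed at practice level". The Sample size section takes the view that "a mean difference of 0.3% in HbA1c change could be considered clinically significant", uses "SD of HbA1c change 1.3" (per cent), and powers the comparison "at four post-treatment occasions" with "a 5% family-wise significance level and Bonferroni correction for multiple testing". It arrives at 463 patients per group after allowing for 10% withdrawal. It then applies a design effect, "assuming 10 patients per cluster and an intra-class correlation coefficient of 0.047", and ends at 659 patients per arm. No number of practices is stated.

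The Data collection section describes who enters the analysis: "Data will be automatically extracted from the EMR of the family physician for all patients who satisfy the eligibility criteria". Under Participants and setting, these are enlisted adults with diabetes identified by code, drug or laboratory result, less two exclusions. No limit or sampling per practice is described.

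On revising the calculation, the Sample size section says: "They can be adjusted after baseline registrations if correct standard deviations and intra-cluster correlation coefficients are known".

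**The concern.** In a cluster-randomized trial a patient count has no fixed power. The same 659 patients carry less information when they come from fewer, larger practices. Here the patient count is the only stated target. The practice size behind it is an assumption that nothing in the conduct of the trial enforces: each practice brings whatever number of eligible patients it has, and practices will differ. Physicians are invited individually while practices are randomized, so one practice may bring the patients of several physicians.

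A team that monitors recruitment against 659 could therefore reach its number with too few practices. The re-sizing clause would not necessarily catch this. It is optional, and it does not name the input that the extraction rule leaves open. The shortage could not be made good later, because more patients from the same practices cannot replace practices missing at randomization.

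**Working it through.** **Inputs from the Sample size section:** difference 0.3, SD of change 1.3, family-wise alpha 0.05 over four tests (0.05/4 = 0.0125 per test, two-sided), power 80%, withdrawal 10%, 10 patients per cluster, ICC 0.047.

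**Reproducing the plan's figure.** The two-sample t-test needs 421 per arm. 421 x 1.1 = 463. The design effect is 1 + (10 - 1) x 0.047 = 1.423, and 463 x 1.423 = 658.8, so 659. The plan's arithmetic is correct. It implies 659/10, or about 66 practices per arm.

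**Power if 659 per arm is held fixed and practice size changes.** With 10% loss, 659 x 0.9 = 593.1 patients per arm are analysed. The effective number is 593.1/DE, with DE = 1 + (m - 1) x 0.047 for equal practices of size m. Power is for the t-test at alpha 0.0125 with that effective number per arm. Apart from 10, the values of m are assumed, because the document gives no other.

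| m | DE | Effective n per arm | Practices per arm at 659 | Power | Practices per arm needed for 80% (463 x DE / m) |
|---|---|---|---|---|---|
| 5 | 1.188 | 499 | 132 | 87% | 110 |
| 10 | 1.423 | 417 | 66 | 80% | 66 |
| 20 | 1.893 | 313 | 33 | 65% | 44 |
| 30 | 2.363 | 251 | 22 | 53% | 37 |

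If the 10% loss also shrinks each practice, DE = 1 + (0.9m - 1) x 0.047. This gives 1.799 at m = 20 and 2.222 at m = 30, with power of about 68% and 56%.

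**Unequal practice sizes.** DE = 1 + [(1 + CV²)m - 1] x ICC. At a mean of 10 and an assumed CV of 0.6, DE = 1 + (1.36 x 10 - 1) x 0.047 = 1.592. The effective number is 593.1/1.592 = 373 per arm, and power is about 74%. Restoring 80% needs 463 x 1.592 = 737 patients per arm, or about 74 practices.

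**Holding practices fixed instead.** With 66 practices per arm and all their patients analysed, power is about 94% at 20 per practice but about 53% at 5 per practice.

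**The case against.** The strongest reply is that the low-power figures need a stopping rule that the article does not contain. The Recruitment section invites every Dutch- and French-speaking family physician using the software, sends reminders and then telephones. The Randomization section allocates the practices that agree. This reads as taking every willing practice. If about 66 per arm joined, practices larger than 10 would raise power. The objection stands, and it means that the direction of any departure from 80% is unknown.

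Practice size is also not given beyond the figure of 10, and the absence of a cap does not show that practices average more. This stands too. Every shortfall above is conditional on an assumed size or CV.

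A reader might infer that re-sizing would use the SD of the HbA1c level, since a baseline registration is cross-sectional. The text does not support that. The only SD the section names is that of change, and the clause most naturally refers to it. It would still help to say so.

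A reader might also infer that the remedy is simply to recruit 66 practices per arm. That number is built on the same 10 patients per practice. It is more than needed with equal practices of 20 or 30, and too few at 5, or at a mean of 10 with marked size variation.

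Finally, the analysis remains valid. The Data analysis section models practices with random intercepts whatever their size, so no estimate or error rate is compromised. An unseen full protocol may give a practice target. But the article itself states the inputs, the target and the extraction rule, and these do not fit one another.

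**Conclusion.** The point holds in limited form. The stated 80% power at 659 patients per arm requires about 10 or fewer patients per practice on average, with little variation in size. The extraction rule does not secure this, the target does not mention practices, and the re-sizing clause does not list practice size.

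If 659 per arm were treated as sufficient, the loss would be about 15 percentage points at 20 per practice (80% to 65%) and about 27 at 30 (80% to 53%). It would be slightly smaller if withdrawal also reduces practice size. Variation alone, at a mean of 10 and CV of 0.6, would cost about 6 points (80% to 74%). All of this holds the ICC at 0.047, alpha at 0.0125 and loss at 10%.

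A reader might conclude that the trial is underpowered, or that exactly 10 patients per practice are required. The document supports neither: it sets no halt at 659 patients, and smaller practices at the same patient total give more power (87% at 5 per practice).

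**What to change.** - State the target as practices per arm as well as patients per arm, using DE = 1 + [(1 + CV²)m - 1] x ICC, where m and CV are the mean and coefficient of variation of practice size in the baseline export.
- Do not fix the target at 66 practices. Compute it from the observed m and CV.
- Add m and CV to the re-sizing clause, and specify that its SD and ICC are those of HbA1c change.
- Judge recruitment on both counts. If fewer practices join than the calculation requires, restate the power they give.

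The cost is a few lines of protocol wording and one recalculation, with no change to the data extracted. The downside is that the stated power may become less favourable. The change should be made before recruitment closes, while practices can still be added.
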